### Control group

The study coordinator will inform the participants about osteoporosis as the potential cause of their fracture. A lay pamphlet on strategies to prevent a secondary FF will be provided, including the recommendation to visit their PCPs and the need for fall prevention and pharmacological intervention in most patients.

### Outcomes and data collection

All participants will be followed for a period of 18 months. A multilevel approach is being used, in which outcomes at the patient level will be measured with quantitative tools, and outcomes at the organization level (*e.g*., perception of the degree of integration and collaboration between organizations) will be measured simultaneously using qualitative techniques [57]. Combining both qualitative and quantitative measures will allow a better understanding and contextualisation of the quantitative results, and verification as to how organization level factors impact the effectiveness outcomes [57,58].

### Quantitative data

With the exception of the first encounter with the participants recruited from the orthopedic clinics and the inpatients from the intervention sites with hip and other fractures, all data will be collected through phone surveys and the participant diary. A baseline questionnaire will be completed by all participants, including demographic data and relevant medical history (*e.g*., height, weight, smoking and drinking history, family history of hip fracture, use of glucocorticoids) and the CaMos questionnaire [59]. The Fracture Risk Assessment Tool (FRAX) score will be used, irrespective of BMD results availability [60]. A Canadian Association of Radiologists and Osteoporosis Canada 10-year absolute fracture risk (CAROC) score will be generated for participants who undergo a BMD test within +/− 3 months of the sentinel event [59,61]. A study exit questionnaire will be administered at the end of the intervention or when the participant withdraws his/her consent to participate.

### Primary outcome

The primary outcome is the incidence of secondary FF during the 18-month follow-up period, including the date of the event, related emergency room visit, and hospitalization. This will be ascertained during quarterly telephone surveys, and confirmed with the participant’s hospital record when possible.

8. Admission to a long-term care facility will be queried during each telephone survey.

9. All participants’ perceptions of care integration will be captured in the exit questionnaire. In the absence of a formally validated instrument to measure the outcome of interest [70], the measurement tool will consist of a customized version of a questionnaire on the perception of care integration from a patient perspective [71]. Five questions, corresponding to the interaction subscale, are being used to investigate this study objective on program integration.

10. Intervention participant’s satisfaction with the FF prevention program will be measured using questions similar to those used by Berendsen *et al*. for their assessment of the sources and amount of information preferred by the participant in the context of an integrated program [72], along with general questions with regards to the participant’s satisfaction with the program.

11. Participants’ expectations and whether they are perceived as met will be collected at the beginning and end of the program. The questionnaire is an adapted version of Gignac’s Program Expectation Scale and uses a 3-point scale ranging from 1 (not at all likely) to 3 (extremely likely) [73]. Participants will also be asked to rate the extent to which they believe the program would produce (before the program) or has produced (end of the program) health benefits for themselves.

12. Individuals who chose to leave the program (or part of it) will be contacted by telephone to document the reason(s) for withdrawing while completing the exit questionnaire.

### Qualitative data

Focus group sessions organized per intervention region will gather a purposeful sample of healthcare managers of fall prevention programs, medical bone specialists, orthopedic surgeons, PCPs and GMF nurses involved in the trial, as well as patients. The sessions are scheduled to last about 60 minutes in length. A maximum of eight professionals will participate per focus group, so sessions with healthcare professionals will be repeated twice for greater participation. The topics and questions of the semi-structured questionnaire will be guided by the conceptual frameworks selected for this project [41,44]. The first session (at baseline) will aim to understand both the factors for success and the potential barriers to the implementation of a FF prevention program. The second session will target the barriers and facilitating factors for maintenance of a FF prevention program, as well as measure the degree of integration between the organizations involved (at 12 months). The two focus groups for the patients (one at baseline and another one between 12 and 18 months post-recruitment) will be geared towards patients’ expectations and satisfaction about the program, as well as perception of integration of care. All focus group sessions will be audiotaped and transcribed.

### Statistical analysis

#### Sample size

##### Quantitative evaluation of entire cohort

Based on preliminary (almost four years follow-up) results from the OPTIMUS project, the incidence of a secondary fracture at 16 months in the control group is expected to be 10%; therefore, this incidence of fracture was used as a proxy for the sample size calculation of this project (primary outcome measured at 18 months). Considering the reported efficacy of antiresorptive drugs among others (average absolute reduction rate of 4%) [74-77], the results obtained in the intervention group of the OPTIMUS cohort (expected absolute reduction rate in FF of 2.5%), as well as the expected synergy with fall prevention programs, and collective orders that will allow for a rapid pharmacological intervention, an absolute reduction of 3% (*i.e*., a secondary fracture incidence at 18 months of 7% in the intervention group) is a conservative estimate of the effect to be detected. Under these assumptions and assuming a power of 80% and an alpha level of 5%, 1,356 participants per group are necessary to verify the primary hypothesis. It is estimated that approximately 15% of the participants will be lost to follow-up or will withdraw from the study prior to the 18-month data collection time point. Therefore, a total of 1,596 participants will be recruited in each group (total N = 3,192).

##### Qualitative focus group analyses

Based on the qualitative literature, it is estimated that 6 to 12 participants are required to achieve study themes redundancy [78,79]. Our targeted sample size should then allow for the saturation of the various barriers to and facilitators of the implementation of an integrated FF prevention program (first sessions’ focus), as well as the qualitative assessment of the intensity of interorganizational collaboration within each intervention site (second sessions’ focus) [80,81].

### Data analysis

#### Quantitative component

Descriptive summaries of baseline participant characteristics in the control and intervention groups will be generated. Any statistical differences (due to selection bias, for example) between the study groups or within a study group (between the different sites) will be tested using chi-square tests or Student’s t-tests (or their non-parametric equivalents if necessary) and accounted for in the following analyses. According to the pragmatic design standards, statistical analysis of the data will follow the intention-to-treat principle; *i.e*., the analysis will include all patients regardless of their compliance with their study group intervention. The implementation process will also be documented with descriptive statistics.

#### Primary outcome

The numbers of participants presenting with a least one secondary FF at 18 months will be compared using a chi-square test. A logistic regression model will be fit to assess the intervention effect, while adjusting for variables thought to influence the outcome and accommodating any imbalance between groups at baseline. The intervention effect and its 95% confidence interval will be generated. Descriptive statistics on the cumulative incidence of recurrent FF will also be generated for each group.

#### Secondary outcomes

Initiation and compliance with pharmacological osteoporosis treatment at 3, 6, 9, 12 and 18 months, and mortality rate will be analysed independently, as for the primary outcome. Time to first fall will be compared between study groups using a time-to-event type of analysis (log-rank test or Gehan-Wilcoxon, depending on the data distribution). A Cox regression model that allows for the adjustment of baseline variables that have been shown to influence the outcome will be used. The difference in the number of significant falls and fall-related hospitalizations will be assessed using a Poisson regression model. Participants’ quality of life and practice of physical activities measured over time will be fit and compared between the two study groups using an analysis of variance (ANOVA) for repeated measures. The total score of the participant’s perception of care integration will be generated for each participant by summing up all questionnaire items. Group scores will be compared using a linear regression model. If numbers allow, a sub-group analysis will be considered among the intervention group to test the effect of provincial versus local fall prevention programs as a covariate on the primary outcome.

The cost-effectiveness ratio will be expressed as the difference in costs between the study groups, divided by the difference in secondary fracture rates between the two groups. Costs will be calculated as the units of resources used in the treatment of a FF, multiplied by the cost of one unit. The uncertainty concerning the incremental cost, the incremental effectiveness, and the incremental cost-effectiveness ratio will be estimated by conducting probabilistic analysis through non-parametric bootstrapping [82]. Results from the bootstrapping exercise will be depicted by cost-effectiveness acceptability curves. All quantitative analyses will be performed with the SPSS 18 software (SPSS, Inc., 2009, Chicago, IL), with the exception of the economic analyses, which will be performed using Oracle Crystal Ball (http://www.oracle.com/us/products/applications/crystalball/index.html).

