**Methods/design:**

This pragmatic, controlled trial at 11 hospital sites in eight regions in Quebec, Canada, will recruit community-dwelling patients over age 50 who have sustained a fragility fracture to an intervention coordinated program or to standard care, according to the site. Site study coordinators will identify and recruit 1,596 participants for each study arm. Coordinators at intervention sites will facilitate continuity of care for bone health, and arrange fall prevention programs including physical exercise. The intervention teams include medical bone specialists, primary care physicians, pharmacists, nurses, rehabilitation clinicians, and community program organizers.

The primary outcome of this study is the incidence of secondary fragility fractures within an 18-month follow-up period. Secondary outcomes include initiation and compliance with bone health medication; time to first fall and number of clinically significant falls; fall-related hospitalization and mortality; physical activity; quality of life; fragility fracture-related costs; admission to a long term care facility; participants’ perceptions of care integration, expectations and satisfaction with the program; and participants’ compliance with the fall prevention program. Finally, professionals at intervention sites will participate in focus groups to identify barriers and facilitating factors for the integrated fragility fracture prevention program.

This integrated program will facilitate knowledge translation and dissemination via the following: involvement of various collaborators during the development and set-up of the integrated program; distribution of pamphlets about osteoporosis and fall prevention strategies to primary care physicians in the intervention group and patients in the control group; participation in evaluation activities; and eventual dissemination of study results.

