### Recruitment

Drawing upon the methodology of previous studies in a similar population [32-34,55], participants for intervention sites will be recruited by a study coordinator over a period of 12 months, and will provide their informed consent to participate and complete the baseline questionnaire. Three methods will be used to recruit intervention group participants:

1. Patients with FFs in participating outpatient orthopedic clinics will be identified by a study coordinator;

2. Hip fracture inpatients will be approached on the ward during their hospitalization;

3. And hospital emergency and ward discharge administrative data will be scanned for patients with a primary discharge code typical of a FF. These participants will be contacted by mail by the hospital to inform them about the research project and that a local study coordinator will contact them. Electronic discharge data allows patient identification within one week following discharge.

Due to budgetary and ethical considerations, only strategy 3 will be used to recruit participants in the control hospitals/regions. Should it be required as an alternative, FF patients’ identification through the *Régie de l’assurance maladie du Québec* (RAMQ) database will be considered, as in the Recognizing Osteoporosis and its Consequences in Quebec (ROCQ) study [55]. The main limitations of this alternative strategy as well as strategy 3 are a delay required to obtain patients’ information (estimated at two months in the case of the RAMQ data, one week for the hospital administrative data), and a potential selection bias (those more at risk for fractures, or who are younger and more educated may be more likely to consent); however, such strategies might be an efficient way to increase the external validity of the study by recruiting a broader range of fracture patients.

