## Discussion

This trial is testing a comprehensive, integrated secondary FF prevention program in a real-life setting, and is designed to optimize translation of research evidence into practice [93-95]. The pragmatic evaluative design of this project, rooted in the Canadian Institutes of Health Research Integrated Knowledge Translation process [96], will provide estimates of the effectiveness of a FF prevention program in different socioeconomic contexts, thereby increasing the generalizability of the results.

FF prevention is needed for much longer time periods than the length of this study, and the creation of a cohort of patients who have experienced FFs offers an opportunity to further address continuity and gaps regarding integrated FF prevention programs. The study team is seeking funding for continuing research, including follow-up at five years.

A limitation of this study lies in the recruitment strategies. Patients in the control group, identified through administrative databases, may present with more severe risk factors, which translate into a higher likelihood of a secondary FF. This may create a selection bias between the recruiting sites, which will be accounted for in the statistical analyses. In the intervention group, a surveillance bias for secondary FF is possible, since this group is sensitized to FFs. This may reduce the observed study effect; however, the large size of this trial, based on conservative effect estimates, should provide sufficient power to detect the intervention effect, if present. Finally, control sites/regions will be monitored throughout the trial to identify emerging fall prevention programs. This will be accounted for in the statistical analysis should participants take part in these programs. Another limitation related to the external validity of this study lies in the organizational variations between participating regions. However, the qualitative component of the study should shed light on those variations and help in a more accurate interpretation of the results.

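### The cost-effectiveness ratio has no baseline adjustment in either term, so in this site-allocated trial it may reflect case mix as well as the program

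*Protocol article*

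**What the plan says.** Under Data analysis, Secondary outcomes, the protocol article states: "The cost-effectiveness ratio will be expressed as the difference in costs between the study groups". For the denominator, it says that this numerator is "divided by the difference in secondary fracture rates between the two groups". Costs are resource units used in treating a fragility fracture times unit cost. Uncertainty in the incremental cost, the incremental effectiveness and the ratio "will be estimated by conducting probabilistic analysis through non-parametric bootstrapping". The economic work runs in different software from the other quantitative analyses.

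The two arms are not exchangeable by design. The Abstract says patients are recruited "to an intervention coordinated program or to standard care, according to the site". Intervention sites use three recruitment routes, while under Recruitment "only strategy 3 will be used to recruit participants in the control hospitals/regions". The Discussion says controls "may present with more severe risk factors, which translate into a higher likelihood of a secondary FF", and adds: "This may create a selection bias between the recruiting sites, which will be accounted for in the statistical analyses".

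For the primary outcome, the article specifies a logistic model fitted "while adjusting for variables thought to influence the outcome and accommodating any imbalance between groups at baseline". The opening paragraph of the Quantitative component says that baseline differences between groups or sites will be tested for and taken into account in the analyses that come after it.

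**The concern.** A difference between site-allocated groups recruited by different routes mixes the program's effect with case mix. If controls carry more baseline risk, part of the fracture difference in the denominator is selection. The same excess fractures raise control costs, which lowers the incremental cost in the numerator. The bootstrap describes sampling error around whatever quantity is computed and does not remove confounding from it.

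Cost-effectiveness is part of the overarching aim and of the second secondary question. The results are to go to ministry and public-health decision makers to promote wider coverage of the program. If the clinical effect is adjusted and the ratio is not, the two conclusions rest on different estimates of the same fracture effect.

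**Working it through.** **Inputs.** From Sample size: control risk 10%, intervention risk 7%, difference 3 points, power 80%, alpha 5%, loss 15%. The article gives no costs, so no ratio can be computed, only the factor by which it would change. Every selection or ascertainment figure below is an assumption.

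**1. The plan's own figure.** With pooled variance, two-sided alpha and no continuity correction:

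n = [1.960 × √(2 × 0.085 × 0.915) + 0.842 × √(0.10 × 0.90 + 0.07 × 0.93)]² / 0.03² = (0.773 + 0.331)² / 0.0009, which on unrounded values rounds up to 1,356.

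1,356 / 0.85 = 1,595.3, rounded up to 1,596. Both stated figures reproduce, so 10% and 7% are a fair like-for-like base.

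**2. Effect of case mix on the denominator.** Let d be the like-for-like risk difference and b the excess control risk due to selection. An unadjusted difference is d + b. With a fixed, positive cost difference, the ratio is multiplied by d / (d + b).

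- b = 1 point (assumed): 0.03 / 0.04 = 0.75
- b = 2 points (assumed): 0.03 / 0.05 = 0.60

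**3. The same on an odds scale.** Multiply the control odds (0.10 / 0.90) by an assumed case-mix odds ratio and subtract 7%. Factors are 0.03 divided by the unrounded difference.

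| Assumed odds ratio | Control risk | Difference (points) | Factor on ratio |
|---|---|---|---|
| 1.1 | 10.9% | 3.9 | 0.77 |
| 1.2 | 11.8% | 4.8 | 0.63 |
| 1.3 | 12.6% | 5.6 | 0.53 |
| 1.5 | 14.3% | 7.3 | 0.41 |
| 0.8 | 8.2% | 1.2 | 2.58 |

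The last row shows the reverse case, with lower-risk controls.

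**4. The numerator.** Write P for the program cost per participant and F for the cost of a fracture. The cost difference is P − F × (difference in risk), so the ratio is P / (difference in risk) − F. For positive P it falls as the risk difference grows. Excess control fractures therefore move both terms the same way.

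**5. An opposing bias.** The Discussion also says that surveillance bias in the intervention group may reduce the observed effect. If 20% over-ascertainment is assumed there, 7% is seen as 7% × 1.2 = 8.4%. For case-mix odds ratios of 1.0, 1.1, 1.2 and 1.3, the observed differences are 1.6, 2.5, 3.4 and 4.2 points. The first two lie below the true 3.0 and the last two above it, so the net direction is open.

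**6. Does the primary model already supply the denominator?** Not directly. Logistic regression yields an odds ratio, while the ratio needs a difference in risk. Moving from one to the other takes a standardisation step that the economic paragraph does not mention. The primary model also says nothing about an adjusted cost difference.

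**The case against.** The strongest reply is that the economic paragraph gives only the generic definition of an incremental ratio, which is valid with adjusted or unadjusted inputs. A reader might infer that the protocol prescribes a crude ratio. It does not use that word or an equivalent. The Quantitative component and the Discussion both commit to accounting for selection differences, and the economic analysis is among those that follow. On this view all that is missing is detail that an article may leave to a fuller plan.

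Part of this stands: the intent to adjust is documented, and the absence of adjustment is an inference from the formula. The general commitment still does not settle the matter. In the Quantitative component it depends on differences found by testing. The one specific economic instruction takes plain group differences and bootstraps them in separate software. The adjusted model that is specified does not produce either quantity the formula needs.

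A reader might also infer that the ratio is bound to flatter the program. The documents do not support that. The Discussion says controls may be at higher risk, not that this is expected. Surveillance bias is named as working the other way. Recruitment notes that those who consent through the control route may be younger and more educated as well as more at risk. Only intervention sites approach hip-fracture inpatients on the ward, and the Background describes hip-fracture patients as at high risk of another fracture.

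**Conclusion.** The point holds in a limited form. The stated formula and bootstrap contain no adjustment in either term, in a design where the article itself raises selection differences, and its general promises are not carried into the ratio. Computed as written, the ratio may be biased. It favours the program if controls are at higher risk, and it may go the other way under surveillance bias or a different case mix.

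The factors 0.75 to 0.60 illustrate sensitivity and are not estimates. They rest on an assumed 1 to 2 points of excess control risk, a true difference of 3 points, and a fixed, positive cost difference. If the program saved money, a factor on cost per fracture avoided would have no simple meaning. A reader might infer an expected understatement of 25% to 40%, but nothing in the document anchors the assumed excess.

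The documents also do not support requiring whole sites to be resampled. With six intervention and five control sites, that is debatable and is not part of this point.

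**What to change.** In the economic paragraph under Data analysis, Secondary outcomes:

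- Define incremental effectiveness as the standardised (marginal) risk difference from the adjusted primary-outcome logistic model.
- Define incremental cost as a cost difference adjusted for the same baseline covariates.
- Re-estimate both in every bootstrap sample, so that the intervals and acceptability curves describe the adjusted quantities.
- Report the unadjusted ratio alongside, so that readers can see how much the adjustment matters.

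The cost is additional programming, with no new data. The adjusted ratio may be less favourable or less precise. Only measured confounding is removed: unmeasured differences between sites and unequal detection of fractures would remain and should be stated as limits.
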